#### **6.2.8. Randomization**

The randomization list will be created by a statistician from the clinical research department of Nantes university hospital. Randomization will be performed using blocks and a ratio of 1:1.

A sealed envelop that contains the randomization # and the group affiliation will be created for each patient. These envelops will be numbered and stored in each participating center. Each time a patient is included, the investigator will take the next envelop, following the numerical order.

## **7. VIGILANCE AND MANAGEMENT OF SIDE EFFECTS**

### **7.1. DEFINITIONS**

#### **7.1.1. Unexpected event**

An unexpected event is defined by any harmful manifestation that occurred to a patient or an individual enrolled in a study, and that is not associated with the method tested.

Any unexpected event encountered during the study, observed by the physician or reported by the patient, will be documented in the patient file in a dedicated section.

The categorization of the unexpected event will be displayed according to this scale :

1 = benign

2 = moderate

3 = severe

4 = vital prognosis at stake

#### **7.1.2. Unexpected side effects**

A side effect is suspected when an unexpected event that may be caused by the procedure tested, whatever this link is doubtful, plausible, possible or certain.

#### **7.1.3. Severe event or side effect**

An unexpected event or side effect is qualified as severe if it:

- \* leads to the patient's death,
- \* impacts the vital prognosis (for example led to the transfer in intensive care unit)
- \* triggers an incapacity or an invalidity, either temporary or permanent
- \* increases the hospital length of stay,
- \* is responsible of a congenital or neonatal abnormality,
- \* requires a specific medical care to prevent the degradation of the patient's state to any of the above situation.

#### **7.1.4. Expected events or side effects**

An expected event or side effect is an event that has been anticipated (and mentioned) in association with the disease studied.

Reminder : Severe expected side effects or events will be declared by the study sponsor to the corresponding authorities.

### **7.1.5. Unexpected side effect**

An unexpected side effect is an effect whose nature, severity, frequency or evolution doesn't match the information related to the procedures tested during the study.

Reminder: Unexpected serious side effect will be declared to the competent authorities within 7 or 14 days after the information of the sponsor.

## **7.2. LIST OF THE EXPECTED EVENTS OR SIDE EFFECTS**

### **Associated with the procedure tested:**

Common undesired events for the « early » and the « progressive » procedures:

In this case the causation of the event by the procedure is considered if it occurs within the first minutes after it started. Outside of this temporal definition, the undesired event will be associated with the evolution of the disease.

- Nausea/Vomiting
- Headache
- Neurological worsening (aggravation of the existing deficits or occurrence of new ones)
- Blood pressure surge persistent on a second measurement, with a BP increase of at least 40mmHg and above 180/100
- Sensation of passing out (linked to a vagal reaction (bradycardia, nausea, sweating) / Hypotensive / other)
- Fall that can be associated with traumatic brain injury or other orthopedic complications (fracture, luxation, sprain)

« Progressive arm »: Complications linked to immobility

- Deep vein thrombosis,
- Pneumopathy
- Urinary tract infection,
- Constipation,
- Sores,
- Swallowing disturbances

“Early arm” Neurological worsening (aggravation of the existing deficits or occurrence of new ones)

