#### ➤ Risks associated with the procedure studied

Major side effects could be observed:

- Neurological worsening defined by aggravation of the existing deficits (motor, aphasia,..) or occurrence of new neurological deficits during or within the first 5 minutes after upright positioning.
- Fall that can be complicated by fracture

A complete list of the side effects can be found in the vigilance section (see infra).

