#### Secondary outcome

- Clinical score (neurological deficit) based on the NIHSS at 7 days and 3 months: comparison of the mean scores between the two groups using a Student's test.
- Functional scale (Rankin score) at 7 days: comparison of the proportions of patients with a score [0-2] by a Chi square test.
- Autonomy scale (Barthel index) at 7 days and 3 months: comparison of the proportions of patients with a score < 60 (dependent) between the 2 groups using a Chi square or a Fisher test
- Length of stay: comparison of the means between the two groups using a Student's test
- Percentage of patient back home before 7 days or 3 months: Chi square test or Fisher test.
- Side effects associated with sitting in the two groups (tolerance of upright positioning in the early versus progressive arms) : description of the side effect in the 2 groups and comparison of the most frequent (>5%) by a Chi square test or a Fisher test.

- Prevalence of swallowing disturbance, pneumopathy, acute urinary retention, bladder catheterization, deep vein thrombosis during hospitalization: comparison between the two groups using a Chi square test or a Fisher test.
- Prevalence of post stroke fatigue: comparison between the two groups using a Chi square test or a Fisher test.

A multivariate logistic regression model will be used in a second step to adjust on age and former (before the qualifying event) Rankin score.

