### **6.2.2. Statistical justification for the number of patients required**

In a meta-analysis of two pilot studies comparing an « early » to a « usual » mobilization procedure, Craig and coll. (9) showed that the percentage of patients with a Rankin score [0-2] was 34.7 % at 3 months in the « usual » group (n=49) versus 57.4 % in the « early » group (n=54).

In our study, we hypothesized that the functional outcome at 3 months assessed by the Rankin score will be better in the « early » group than in the « progressive » group, with a percentage of Rankin [0-2] of 35% in the « progressive » group and 50% in the « early » group. With an alpha risk of 5% and a power of 80% (bilateral), 183 patients per group are required to show a difference. Total number will then be 366 patients.

Percentage of poor tolerance during the first sitting is estimated between 5 and 10% in the 2 groups. As this may affect the Rankin score at 3 months, the number of patient to include has been increase to 400.

If the superiority of the « early » group is not statistically demonstrated, a switch to non inferiority could be undertaken. For this analysis, the non inferiority threshold is set at -5 % (maximum acceptable clinical difference). With 400 patients, non inferiority will be demonstrated if the real difference between the two groups is between 9 and 15%.

Reference: Committee for Proprietary Medical Products (CPMP). Points to consider on switching between superiority and non inferiority. 2000. European Medical Agencies (AMEA). CPMP/EWP/492/99.

The study will be undertaken in 11 centers. Each one, has the potential to recruit patients, with at least 300 cerebral infarction cases a year.

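### Section 7.2 applies different attribution and expectedness rules to the two arms for neurological worsening and for three immobility complications

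*Protocol*

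**What the plan says.** Section 7.2, under the part on events associated with the procedure, has three layers.

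- **Common list, both arms.** It includes neurological worsening. The procedure is held responsible only if the event falls in the first minutes after it starts. For anything later: "Outside of this temporal definition, the undesired event will be associated with the evolution of the disease".
- **Progressive arm only.** "Complications linked to immobility", namely deep vein thrombosis, pneumopathy, urinary tract infection, constipation, sores and swallowing disturbances. No window is given.
- **Early arm only.** Neurological worsening, a second time, with no window.

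A separate list of disease-related events, not split by arm, follows. It contains worsening, deep vein thrombosis, pneumopathy and swallowing disturbances. It does not contain urinary tract infection, constipation or sores.

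Other sections bear on how this list is used. Section 1.2.2.1 refers to the vigilance section for the complete list of side effects. It defines procedure-related worsening as occurring during positioning or in the 5 minutes after it, without distinguishing the arms. Section 7.1.5 calls a side effect unexpected when it is "an effect whose nature, severity, frequency or evolution doesn't match the information related to the procedures tested", and sets 7 or 14 days for declaring serious ones. Section 6.2.1 plans a "description of the side effect in the 2 groups" with tests of the most frequent ones and, as a separate item, a between-arm test of several complications during hospitalization.

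**The concern.** Whether an event is charged to the procedure, and whether it is expected, should depend on the event and its timing. In section 7.2 it depends partly on the arm label, and the trial is open, so whoever codes the event knows the label.

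This touches the risk that the protocol itself calls the main one: section 1.2.3 names neurological worsening. Section 5.4.3 allows the study to stop early if early sitting proves harmful, and section 6.2.4 gives no statistical stopping criterion. That judgement would therefore rest on safety information, including what the independent security committee sees under section 7.3.2. If late worsening is charged to the procedure in one arm and to the disease in the other, the safety picture shifts against early sitting for a reason unrelated to the patients. Expectedness shifts too, because three complications are anticipated in one arm and on no list for the other.

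**Working it through.** No planned figure depends on section 7.2, so the check sets the passages side by side.

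**1. Where each event is listed**

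| Event | Procedure list, progressive arm | Procedure list, early arm | Disease list, both arms |
|---|---|---|---|
| Neurological worsening | Common list, first minutes only | Common list, first minutes only, plus a separate entry with no window | Yes |
| Deep vein thrombosis, pneumopathy, swallowing disturbances | Arm-specific entry, no window | Not listed | Yes |
| Urinary tract infection, constipation, sores | Arm-specific entry, no window | Not listed | No |

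**2. Attribution of worsening.** Take a worsening several hours after positioning.

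- Progressive arm: the common rule sends it to the disease. The 5-minute definition in section 1.2.2.1 agrees.
- Early arm: the common rule and section 1.2.2.1 again point to the disease, but the separate entry places it under the procedure.

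The protocol thus gives one answer for the progressive arm and two for the early arm. The window itself is also stated in two ways: first minutes in section 7.2, and 5 minutes in section 1.2.2.1.

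**3. Expectedness.** Take a urinary tract infection that prolongs the stay, which makes it severe under section 7.1.3. Under section 7.1.2 even a doubtful link to the procedure is enough for a suspected side effect.

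- Progressive arm: it is listed, hence expected. Section 7.1.4 has the sponsor declare severe expected events but states no time limit.
- Early arm: it is on neither list, hence unexpected, and the 7- or 14-day limit of section 7.1.5 applies.

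The difference lies in classification and timing, not in whether a declaration is made at all. Section 7.3.1 adds an ambiguity: it exempts from the notification form events described earlier. If that means section 7.2, a listed event could be exempt in one arm and notifiable in the other.

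**4. Which analyses are reached**

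- *Complication comparison (6.2.1).* Complications are recorded at hospital exit in all patients (5.2), and the test counts them regardless of attribution. It is not affected.
- *Sitting side effects (6.2.1).* The data come from the sitting procedure and the first sitting (5.1.2, 5.2, 5.3). Immobility complications need not enter. Worsening can enter, and the separate early-arm entry leaves its definition unclear.
- *Primary outcome.* The penalty rule in 6.2.5 and the per-protocol exclusion in 6.2.7 do not refer to section 7.2. The sample size does not use it.

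**5. Direction and size for worsening.** Section 4.1 gives 400 / 2 = 200 patients per arm. Let the true worsening rate be w in both arms, and let a share s of events fall inside the window. If the early-arm entry is read without a window, the counts attributed to the procedure are:

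- early: 200 × w
- progressive: 200 × w × s
- difference: 200 × w × (1 − s)

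The difference is against early sitting and vanishes only if s = 1. The protocol gives neither w nor s, so no number follows.

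**The case against.** The best defence is that section 7.2 is a vigilance list and not an endpoint definition. Tolerance is measured around the sitting, complications have their own outcome in both arms, and section 7.1.2 leaves causality to a judgement on each case. On this view the second early-arm line for worsening is a harmless repeat, governed by the common window and by section 1.2.2.1.

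Much of this stands. The complication comparison is sound, and a redundant repeat is a plausible reading of the early-arm line. But section 7.2 does not say that the common window covers that line, and an unwindowed entry placed after a windowed one can equally be read as an exception. The defence also leaves untouched the three complications that are on no list for the early arm.

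A reader might go further and infer a large artificial difference. The protocol's background figure of 25.3% with at least one complication gives 200 × 0.253 ≈ 51 progressive patients charged to the procedure, against 0 early patients. The documents do not support this. No planned analysis counts immobility complications attributed to the procedure, and deep vein thrombosis, pneumopathy and swallowing disturbances are also on the disease list for everyone, so section 7.2 does not force them onto the procedure. A p-value for such a contrast would belong to no analysis in the plan.

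**Conclusion.** The point holds as an inconsistency in the safety rules. Section 7.2 states attribution of worsening in a way that differs by arm and conflicts with its own common rule and with section 1.2.2.1. It also makes urinary tract infection, constipation and sores expected in one arm only. What is exposed is the attribution of worsening in safety counts and committee review, and the classification and timing of declarations.

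It does not follow that the planned complication comparison, the primary outcome or the sample size is biased. The direction for worsening (more charged to early sitting) rests on reading the early-arm entry without a window and on at least some worsening falling outside it. Its size cannot be stated from the protocol. The expectedness point rests only on the lists as written, and matters when a serious event is suspected of being linked to the procedure. It should be corrected, since the correction is simple and the event concerned is the trial's declared main risk.

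**What to change.** - Reconcile section 1.2.2.1 with both lists in section 7.2, so that there is one list of expected events, one attribution rule and one time window, the same for both arms.
- Delete the separate early-arm entry for neurological worsening, or state that the common window applies to it.
- List the immobility complications, including urinary tract infection, constipation and sores, as expected events in both arms.
- State in section 6.2.1 that immobility complications are reported only under the complication outcome and not among sitting side effects. That sentence should name the events: section 2.2.2 includes urinary tract infection while the test list in 6.2.1 names acute urinary retention, and constipation and sores are in neither.

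The cost is wording in sections 1.2.2.1 and 7.2 and a sentence in 6.2.1. No extra data are needed, because section 5.2 already has immobility-related complications recorded for all patients at hospital exit.

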### **Associated with the pathology :**

- Nausea/Vomiting
- Blood pressure surge persistent on a second measurement, with a BP increase of at least 40mmHg and above 180/100
- Sensation of passing out (linked to a vagal reaction (bradycardia, nausea, sweating) / Hypotensive / other)

- Fall that can be associated with traumatic brain injury or other orthopedic complications (fracture, luxation, sprain)
- Neurological worsening (aggravation of the existing deficits or occurrence of new ones)
- Seizure
- Alteration of consciousness
- Coma
- Death in direct association with the disease (extension of the infarcted zone, cerebral hemorrhage, cerebral edema, herniation), or indirectly linked to the disease (cardiac failure, lung embolism, sepsis, pneumopathy with hypoxia,...)
- Headache
- Swallowing disturbances
- Pneumopathy
- Deep vein thrombosis

**In association with other comorbidities:**

Comorbidities can alter the clinical state of the patient, notably through ischemic cardiopathy or diabetes, that are frequently encountered in the stroke patients.

**In association with the on going therapies:**

Drugs taken by the patient can also have their own side effects. In this situation the referring document will be the summary of product characteristics available on the AFAASAPS website.

### **7.3. MANAGEMENT OF SEVERE SUSPECTED UNEXPECTED ADVERSE REACTION**

#### **7.3.1. Notification of severe events or side events**

Any serious undesired event, expected or not, (unless described above) will be notified through a specific form. The investigator will be responsible to give a detailed and precise report. A severe undesired event must be immediately reported (within 24 hours) to the sponsor by fax (Clinical research department, CHU de Nantes [contact]).

After reception, the sponsor will report the event to the authorities. Once a year, a security report will be edited.

Precision :

- Hospitalization is not an unexpected event per se, it is a criteria for seriousness when motivated by a deleterious clinical event. Scheduled hospitalization is not considered as a severe event. Also only hospitalization > 24h will be declared as a severe event.
- Death is a severe event itself and also a criteria for severity, but it is important to precise the cause of the death to interpret the risk/benefit data
- The criteria « vital prognosis at stake » implies the patient transfer to an intensive care unit

### **7.3.2. Independent security committee (ISC)**

The ISC is a consultative committee in charge of giving its opinion to the sponsor and the principal investigator regarding the security of the study. Its members are experts in clinical research (pathology and methodology) and are not involved in the study otherwise. They are in function for the study duration and are also committed to respect data confidentiality. The designation of the ISC members is collegial between the PI and the sponsor. The ICS receives the annual report on security and can be activated if a severe event or side effect requires further analysis, or if there any doubt regarding the risk/benefit ratio of the study.

### **7.4. MODALITY AND FOLLOW UP OF THE PATIENTS IN CASE OF UNEXPECTED EVENT OR SIDE EFFECT**

In case of serious SUSAR that led to the patient exiting the study, the patient will be followed up until resolution of the adverse reaction.

## **8. ADMINISTRATIVE AND REGULATORY ASPECTS**

### **8.1. ACCESS TO THE DATA AND THE ORIGINAL DOCUMENTS**

The medical data of each patient will only be transmitted to the sponsor or any person approved by it, and eventually to the competent authorities if the confidentiality is warranted.

The sponsor can ask for a direct access to the patient file to verify the compliance to the protocol and data, respecting the confidentiality and within the limits set by the legislation.

Collected data could be treated electronically in compliance with the legislation and the CNIL recommendations (reference MR001).

### **8.2. MONITORING**

The monitoring of the study will be performed by the clinical research department. A clinical research assistant will regularly go to each center to verify the quality of the data reported in the patient file.

This protocol has been classified according to the risk level for the patient:

Category B : expected risks close to the usual care ones

Monitoring visits will be organized by appointment with the investigator. Clinical research assistant will consult:

- the patient file,
- the nurse patient file,
- the patient study file (CRF).

### **8.3. INSPECTION / AUDIT**

Could be organized if needed.

### **8.4. ETHICAL CONSIDERATIONS**

#### **8.4.1. Written Informed consent**

Each Investigator commits to inform the patient in a clear and accurate way, and ask for an written informed consent (informed consent documents in appendix). He will give the patient an information note and a consent form. The patient can only be included in the study after reading and understanding the information and consent forms, signing and dating the consent form.

The investigator will also sign and date the consent. Those documents will be processed in duplicate so that both the investigator and the patient can have one. The one kept by the investigator will be stored in a specific binder for the study.

This protocol can be used in emergency situation. In particular, when the patient shows aphasia, the information and the consent can be provided by a relative or a person who has a close connection to the patient (in accordance with law L. 1122-2 of the “code de la sante publique”). A specific information and consent form has been made. (appendix # 7 et 9). In case of emergency and if the patient is not able to provide his/her consent, this procedure can be used. The patient will be informed at the earliest possible time, and his written consent will be collected in order to continue his participation. This consent from a relative could be collected through a phone call, and signed within 24 hours. Indeed, this study deals with an emergency situation, and the patient needs to be randomized quickly. In the case of a patient with aphasia, who won't be able to give an informed consent the inclusion wouldn't be possible, as the family is usually not present at the time the physician visits the patient. Therefore this may create a bias in the study, as aphasia is observed in about 30% of the stroke patients.

As this is a medical research about a procedure and not a drug, and considering that the study can be easily explained over the phone, the consent may be obtain from the family in that fashion.

If this procedure is using, the investigator must write it down in the patient's file (consent obtained by calling the relative)

The sponsor commits to submit the study protocol to the ethics committee. Information about the modality and the nature of the study, and the guaranties to protect the patient enrolled in the study will be transmitted.

## **8.5.     *AMENDMENTS***

Amendments will be addressed by the sponsor for authorization and information to the relevant committee: AFSSAPS and /or au IRB in accordance with the legislation law 2004-806 of august 9th 2004. The modified protocol will be updated in a dated version. If needed, information letter and consent will also be modified.

## **8.6.     *DECLARATION TO THE AUTHORITIES***

Authorization for this protocol will be required from the AFAASAPS.

